### Recruitment {15}

Patients in the OPD of Prosthodontic and Crown and Bridge Department of Sharad Pawar Dental College and Hospital DMIMSU Sawangi Meghe Wardha were recruited.

## Assignment of interventions: allocation

### Sequence generation {16a}

Computer-generated random numbers

### Concealment mechanism {16b}

On-site computer system

### Implementation {16c}

The co-investigator of the department will generate the allocation sequence, will enrol participants, and will assign participants to interventions.

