## Assignment of interventions: blinding

### Who will be blinded {17a}

Trial participants, outcome assessors, and data analysts

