### Procedure for unblinding if needed {17b}

Data analysis from spreadsheets of random numbers was done to determine the assignment; there is no human involvement; and the process is fully concealed from both study investigators and prospective participants until the study arm is assigned.

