### Data management {19}

Electronic data management will be done; the primary investigator will collect the data and will enter the data into the database for screening and randomisation purposes.

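### One co-investigator generates the sequence, enrols and assigns, which contradicts the claim of no human involvement and leaves concealment from the enroller unsecured

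*Protocol article*

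**What the plan says.** The article spreads its account of allocation over several short entries.

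- Sequence generation {16a} consists of one phrase: "Computer-generated random numbers".
- For concealment, the entry at {16b} is equally brief: "On-site computer system".
- The division of tasks is set out at {16c}, which reads: "The co-investigator of the department will generate the allocation sequence, will enrol participants, and will assign participants to interventions".
- Who will be blinded {17a}: "Trial participants, outcome assessors, and data analysts".
- Procedure for unblinding {17b}, which describes allocation rather than unblinding: "Data analysis from spreadsheets of random numbers was done to determine the assignment", followed by the assurance that "there is no human involvement; and the process is fully concealed from both study investigators and prospective participants until the study arm is assigned".
- Data management {19}: "the primary investigator will collect the data and will enter the data into the database for screening and randomisation purposes".

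The steering committee list {5d} includes a statistician and a data manager. Neither is given a part in allocation. Trial status says that recruitment began in September 2022 and should end at about January 2024.

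**The concern.** Allocation concealment means that whoever decides on a patient's entry cannot know the next assignment. The usual safeguard is to separate the person who makes the list from the person who enrols. {16c} joins these tasks in one role and adds the assignment itself, while {17b} assures the reader that investigators cannot see the process at all.

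The stakes are specific to this trial. Eligibility {10} admits extraoral defects up to 9 × 12 cm in patients aged 10 to 70 years, so cases can differ widely. The size and site of a defect are visible at screening and plausibly affect how accurately an impression can be made, and accuracy is what the objectives compare. An enroller who knew the next arm could, deliberately or not, bring easier defects forward for one method. The article also expects practical advantages from photogrammetry (Rationale and Outcomes {12}), so a prior preference is conceivable. Blinding the assessors does not address selection that happens before assignment.

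**Working it through.** No arithmetic bears on this point. It does not depend on the sample size, the significance level or any rate. The check is to set the entries side by side.

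1. **Who acts.** {16c} names one role for three tasks: making the sequence, enrolling and assigning. {17b} says no human is involved. These are opposite statements about the same process.

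2. **Who is kept from knowing.** {17b} says that study investigators do not know the arm until it is assigned. The co-investigator is a study investigator, and under {16c} makes the sequence. Both can be true only if the sequence is produced in a form its maker cannot see.

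3. **Does {16b} supply that condition?** It names an on-site computer system and nothing more. It does not say who has access, or that an assignment is released only after enrolment is recorded. {17b} gives the source of assignments as spreadsheets of random numbers. A spreadsheet can be read by whoever made it unless access is restricted, and no restriction is stated.

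4. **Does {17a} help?** The blinded groups are participants, outcome assessors and data analysts. The co-investigator is not among them.

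5. **Does {19} help?** It has the primary investigator "will enter the data into the database for screening and randomisation purposes". That is compatible with a computer issuing the arm and does not contradict {16c}. It conflicts with {17b} only if the denial of human involvement is read literally. It is minor support, but it is a further entry to bring into line.

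6. **Is this merely a detail left to a fuller document?** No. The article states who does what and puts all three tasks on one person. An analysis plan could not change that, because allocation is trial conduct.

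Result: {16c} and {17b} contradict each other, and no other entry reconciles them or separates the list-maker from the enroller.

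**The case against.** The strongest reply is that the article does claim concealment and names a mechanism for it. A person can start a computer routine that never displays the list, and a system of that kind could make {17b} substantially true even with the co-investigator at the keyboard. This stands as far as it goes. A reader might infer from {16c} that allocation is not concealed, or that the enroller can foresee every assignment. The documents do not support that: both readings presume access to the list, which the article neither states nor excludes. What the reply does not do is remove the contradiction or supply the missing lock.

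A reader might also want a number for the resulting bias. Any such number would need an assumed shift in case difficulty between arms, and nothing in the article supports one.

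Nor should one infer that the analysis would be helpless. Defect size and site can be recorded at baseline and adjusted for, and {20c} mentions using baseline imbalance to inform multivariable models. Such adjustment would be partial, since it reaches only what is recorded.

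Finally, {16a} and {16b} say nothing of blocking, stratification or planned arm sizes. An article may leave these to the full protocol, so no criticism is made of them here.

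**Conclusion.** The point holds in this form: {16c} and {17b} contradict each other on human involvement and on what study investigators can know, and concealment from the enrolling person is not secured by anything the article describes. Selection by visible defect difficulty is therefore possible. It is not shown to have happened.

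The size of any bias cannot be stated from the document. The exposure is structural: every assignment among the planned 45 patients runs through the role described in {16c}.

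The conclusion rests on two readings. The first is that {16c} means what it says, namely one role for all three tasks. The second is that each patient is assigned to one method, as the three groups described in {20b} indicate. The defect is serious because the article gives an assurance of full concealment that its own division of tasks does not support.

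**What to change.** Change {16c} so that a committee member who neither enrols patients nor analyses outcomes generates and holds the sequence. The data manager listed in {5d} is the natural choice. The statistician would be suitable only if someone else analyses the data, because {17a} says that data analysts are blinded. The co-investigator should only enrol.

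Then bring the other entries into line:

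- {16b}: state that the on-site computer releases each assignment only after eligibility and consent are recorded, and that the enroller has no access to the list.
- {17b}: remove the denial of human involvement and describe the process as it will actually run.
- {19}: say what the primary investigator enters for randomisation, and that this gives no sight of coming assignments.

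The cost is a reassignment of tasks among roles already named, plus a protocol amendment; no extra staff are needed. The change protects only later enrolment. Because recruitment has begun, the trial should also document, for patients already assigned, who generated the list, where it was kept and who could see it, and report this with the results. If the system already hides the list from the co-investigator, saying so in {16b} and correcting {17b} would answer much of the concern, though separating the roles remains the cleaner arrangement.

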## Assignment of interventions: blinding

### Who will be blinded {17a}

Trial participants, outcome assessors, and data analysts

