**Methodology:**

1. Patient screening will be done, and the patient will be allocated to three techniques that are the conventional manual method, photogrammetry method, and 3D scanning in a randomised manner

2. The impression of the defect will be recorded by conventional manual method, photogrammetry method, and 3D scanning

3. The defect will be modelled in three ways: first is as per the manual dimension taken on the patient, second is the organisation of photographic image taken with lab standards and third is plotting of point cloud data to generate the virtual 3D model

4. For photogrammetric prosthesis design, finite photos/images will be taken at multiple angles to model the 3D virtual design. With the use of minimum photographs, the 3D modelling can be performed by using freeware, and a mould is obtained

5. The CAD software was used to design the prosthesis, and the final negative mould can be printed using additive manufacturing

6. The mould fabricated by all three methods will be analysed by a software using reverse engineering technology

**Study design**: Randomised control trial

**Duration**: 2 years

**Sample size**: 45 patients

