## Introduction

### Background and rationale {6a}

#### Background

Facial mutilation and deformities can be caused by cancer, tumours, injuries, infections, and inherited or acquired deformities and has the potential to degrade one’s quality of life by interfering with fundamental tasks like communication, breathing, feeding, and aesthetics.

Depending on the type of defect, producing maxillofacial prostheses for the rehabilitation of patients with various defects can be challenging and complex. The prosthesis is used to replace missing or damaged parts of the cranium and face, like the nose, auricle, orbit, and surrounding tissues, as well as missing areas of soft and hard tissue, with the primary goal of increasing the patient’s quality of life by rehabilitating oral functions such as speech, swallowing, and mastication.

Traditional maxillofacial prosthesis impression and fabrication processes include a number of complicated steps that are costly, time-consuming, and uncomfortable for the patient. These rely on the knowledge of the maxillofacial team, dental clinicians, and maxillofacial technician [1].

The foundation of the impression is the keystone for creating a prosthesis. However, this is the most time-consuming and difficult chair-side operation in maxillofacial prosthesis manufacturing since it requires prolonged interaction with the patient. The field of prosthesis fabrication is being transformed by the digital revolution. Digital technology allows for more accurate impression data to be gathered in less time (3 to 5 min) than traditional methods, lowering patient anxiety. Digital impressions eliminate the need for messy impression materials and provide patients with a more pleasant experience [1]. This method bypasses the procedure of traditional gypsum model fabrication. This eliminates the disparity caused by a dimensional distortion of the impression material and gypsum setting expansion. Traditional dental impression processes leave enough room for errors, such as voids or flaws, air bubbles, or deformities. While current technology for prosthesis planning has emerged as an alternative means to improve patient acceptability and pleasure, not only because the end result is a precisely fitted restoration but also because the chair-side adjustments required are reduced [2].

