### Trial design {8}

The randomised control trial will be conducted at the Department of Prosthodontic, Sharad Pawar Dental College, in an isolated setup. The study protocol will be explained to the participating patients. Furthermore, a written informed consent will be obtained from their parents**.**

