## Methods: participants, interventions and outcomes

### Study setting {9}

The study will be conducted at the Department of Prosthodontics Crown and Bridge Sharad Pawar Dental College and Hospital DMIMSU Sawangi Meghe Wardha.

Methodology:Patient screening will be done and the patient will be allocated to three techniques that are conventional manual method, photogrammetry method, and 3D scanning in a randomised mannerThe impression of the defect will be recorded by conventional manual method, photogrammetry method, and 3D scanningThe defect will be modelled in three ways: first is as per the manual dimension taken on patient, second is the organisation of photographic image taken with lab standards and third is plotting of point cloud data to generate the virtual 3D modelFor Photogrammetric prosthesis design: Finite photos/images will be taken at multiple angles to model the 3D virtual design. With the use of minimum photographs, the 3D modelling can be performed by using freeware, and a mould is obtainedThe CAD software was used to design the prosthesis, and the final negative mould can be printed using additive manufacturingThe mould fabricated by all three methods will be analysed by a software using reverse engineering technology

[figure not shown]

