The most frequent approaches for creating 3D virtual models are the following. To begin, 3D scanning is employed, in which the subjects are scanned in three dimensions, and the point cloud data is used to create a virtual digital model.

Photogrammetry is the second method, which uses finite pictures taken from various perspectives to create 3D digital models. When compared to traditional data collection methods, the two methods are non-contact and save time. Though 3D scanning is a quick and accurate process, it has drawbacks such as a high set-up cost and the need for expert labour. Because of these drawbacks, this technology is only used in prosthetic design on a very limited basis. With a little compromise in 3D modelling accuracy, the photogrammetry method can overcome the drawbacks of 3D scanning. It primarily offers advantages such as the usage of freeware for model creation, the ability to handle the method with semi-skilled people, and the ability to produce good results even with a phone camera using standard operating procedures [4].

The initial step in the photogrammetry approach is to collect photos from all angles; after that, post-processing can be done by a professional using photogrammetry software and CAD/CAM tools. The photogrammetrically formed 3D model can then be used to create a mould, which can be compared against moulds fabricated via 3D scanning and traditional methods [5].

Because the prosthodontist may review the digitally scanned impression at the chairside just by magnifying it, any problems can be corrected before the data is sent to the dental laboratory [6]. However, the complete manufacture of the prosthesis using rapid prototyping is expensive, and the final prosthesis creation is fully dependent on the donor anatomy [7].

When compared to a manually modelled prosthesis, a 3D-produced prosthesis made from the mirror image of the undamaged portion or from the donor does not provide improved aesthetics. The art of sculpturing and adding uniqueness into the prosthesis can be added using the traditional wax-up procedure [8]. Other laboratory procedures can be done using the traditional way to keep costs down and make the prosthesis more appealing [9–11]. 

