### Methods for additional analyses (e.g. subgroup analyses) {20b}

#### SPIRIT guidance: methods for any additional analyses (e.g. subgroup and adjusted analyses)

As there are no subgroups in the study, the subgroup analysis will not be carried out. The population will be studied under three groups—conventional impression, 3D scanning, and photogrammetry—so there is no role of subgroups.

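### Section {17a} lists trial participants as blinded, but in a three-group comparison of a physical impression, photographs and a scan, patients will know which method they received

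*Protocol article*

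**What the plan says.** The whole entry under Who will be blinded {17a} is "Trial participants, outcome assessors, and data analysts". It gives no condition and no description of what each party is blind to. Operators are not on the list.

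The section on additional analyses {20b} describes the comparison: "The population will be studied under three groups—conventional impression, 3D scanning, and photogrammetry". The methodology list in the Abstract and under Study setting {9} says that patients are randomly allocated among the techniques. The next item in that list reads "The impression of the defect will be recorded by conventional manual method, photogrammetry method, and 3D scanning", which leaves some doubt whether each patient has one method or all three.

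On what the patient experiences, the Background {6a} says "Digital impressions eliminate the need for messy impression materials and provide patients with a more pleasant experience". The Intervention description {11a} says of scanning and photogrammetry that "the two methods are non-contact and save time". Study setting {9} says of photogrammetry: "Finite photos/images will be taken at multiple angles to model the 3D virtual design". Under Trial design {8}, "The study protocol will be explained to the participating patients".

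Section {17b}, headed as the unblinding procedure, says that the assignment is hidden from investigators and prospective participants up to the point of assignment, and nothing about afterwards.

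**The concern.** Blinding of participants after allocation needs either interventions that look and feel alike or some form of masking. Here the interventions are the impression procedures themselves, carried out on the patient's face, and they differ by design. A statement that participants are blinded therefore looks wrong on its face, and section {17b} suggests that allocation concealment has been taken for blinding.

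The stake is the credibility of outcomes that awareness can affect. Outcomes {12} lists precision, fit, accuracy, functional effectiveness and time. The article also says in advance that digital methods are quicker and more pleasant for patients. If the trial is later reported as participant-blinded, readers and risk-of-bias assessors will give some of these outcomes more protection than they had.

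**Working it through.** No arithmetic applies. The check sets the article's statements side by side.

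**1. What is claimed.** {17a} claims participant blinding without limit. It is a positive statement, so the point does not rest on detail that a condensed article might leave out.

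**2. Number of methods per patient.** Section {20b} divides the population into three groups, and the methodology list has patients randomly allocated. The natural reading is one method per patient.

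**3. Can the patient tell the methods apart?** Three methods give three pairs.
- Conventional against photogrammetry: impression material and prolonged interaction (Background {6a}) against non-contact image capture ({11a}). The article's own description separates them.
- Conventional against scanning: the same contrast, again in the article's own terms. The Background adds a difference in duration, putting digital capture at 3 to 5 minutes.
- Photogrammetry against scanning: both are non-contact. What separates them is the apparatus, since one is a set of photographs from several angles, for which {11a} says even a phone camera can serve, and the other is a 3D scanner. That a patient notices this is an inference, but a strong one, because the study is explained to patients beforehand ({8}).

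**4. Is there a masking device?** The article describes no sham procedure and no dummy impression. {17b} ends its protection when the arm is assigned, and the impression comes after that.

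**5. Which outcomes are touched?** The comparative objective in Objectives {7} is accuracy evaluated with software, and {18a} makes outcome collection a software analysis. What the patient knows does not enter a surface measurement. Time arises in a procedure whose method both operator and patient can see. For functional effectiveness the article does not say who rates it. If the patient does, the rating is open-label. If a blinded assessor does, the assessor's rating can remain blinded.

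**6. Does the text contradict assessor blinding?** Data management {19} says that "the primary investigator will collect the data and will enter the data into the database for screening and randomisation purposes". The stated purpose is screening and randomisation. No section names this person, or anyone else, as the assessor of the software outcome. Nothing here conflicts with the assessor blinding in {17a}.

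**The case against.** The best defence is the other reading of the design. If all three impressions are recorded on every patient, a patient could be unaware which of them led to the prosthesis, and participant blinding would have a real meaning. The methodology wording allows this, and {18a} speaks of prostheses made in all three ways. What stands of this is that the word impossible would be too strong without naming the design. It does not rescue {17a}, because {20b} points to separate groups, and under the alternative {17a} would still have to say what patients are blind to.

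A second defence is that the consequence is small, since the main comparison is a software measurement. That stands, and it limits the point.

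Stronger readings are tempting, and the article does not support them:
- A reader might infer from {19} that the primary investigator assesses outcomes while knowing the allocation. The sentence is limited to screening and randomisation, and no section gives that person the assessor's role.
- A reader might infer that manual and printed moulds can be told apart by sight, so that assessors are unblinded. The article does not say so. Its additive-manufacturing step is not expressly confined to the digital arms, and the measurement is made by software.
- A reader might infer that function is certainly open-label. That depends on who rates it, which is not stated.
- A reader might count missing detail on how assessors are kept blind as a fault. A journal article may leave that to the full protocol.

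The article is also not one-sided about digital methods. {11a} concedes some loss of modelling accuracy with photogrammetry and no aesthetic gain from a 3D-produced prosthesis. The argument from prior expectations therefore carries modest weight.

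**Conclusion.** The point holds for participants. Under the three-group design, which the article favours, no arm is masked to the patient and {17a} claims a property the trial lacks. This is firmest for conventional against either digital method, where the article's own descriptions decide it. For photographs against a scan it rests on the patient noticing the equipment.

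The size is modest: one of the five listed outcomes (time) is open-label, and a second (function) is too if patients report it. Software-measured accuracy is unaffected by what participants know. No breach of assessor or analyst blinding is claimed. The conclusion assumes one method per patient. If every patient has all three, the error becomes an unspecified claim rather than a false one, and the text still needs correcting.

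**What to change.** In {17a}, delete the reference to trial participants and state that patients and operators are not blinded. If all three methods are in fact recorded on every patient, say so in {8} and {9}, and state in {17a} that patients are blind only to which method produced the prosthesis.

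In {12}, describe time, and any patient-reported function, as open-label.

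To support the assessor blinding already claimed, add to {18a} that the software accuracy analysis is run on digital surface files carrying a code instead of the method name, by someone who did not take the impression. This is a safeguard, not the correction of a demonstrated fault.

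The cost is a few sentences, a little file coding by the data manager already listed in {5d}, and the loss of the participant-blinding claim. Sample size and patient procedures do not change.
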